## Abstract

**Abstract:**

**Background:**

A growing evidence base demonstrates that interventions that focus on participation in physical and social activities can assist in preventing and treating both physical and mental health problems. In addition, there is some evidence that engaging in volunteering activities can provide beneficial social, physical, psychological, and cognitive outcomes for older people. This study will use a randomized controlled trial approach to investigate the potential for interventions involving volunteer activities to produce positive physical and psychological outcomes for older people, thereby contributing to the limited evidence relating to the potential for volunteering to provide multiple health effects.

**Methods/Design:**

This randomized controlled trial will involve 400 retired/non-employed individuals in good health aged 60+ years living in the metropolitan area in Perth, Western Australia. Participants will be recruited from the Perth metropolitan area using a variety of recruitment methods to achieve a diverse sample in terms of age, gender, and socioeconomic status. Consenting and eligible participants will be randomly assigned to an intervention (*n* = 200) or control group (*n* = 200). Those in the intervention group will be asked to engage in a minimum 60 min of volunteer activities per week for a period of 6 months, while those in the control group will be asked to maintain their existing lifestyle or take on new activities as they see fit. Physical and psychological outcomes will be assessed. Primary physical outcomes will include physical activity and sedentary time (measured using pedometers and Actigraph monitors) and physical health (measured using a battery of physical functioning tests, resting heart rate, blood pressure, BMI, and girth). Primary psychological outcomes will include psychological well-being, depression, self-esteem, and quality of life (measured using the Warwick-Edinburgh Mental Well-Being Scale, Center for Epidemiologic Studies Depression Scale, the Rosenberg Self-Esteem Survey, and the Global Quality of Life Scale, respectively). Secondary outcomes of interest will include attitudes to volunteering (measured via open-ended interviews) and personal growth, purpose in life, social support, and self-efficacy (measured using the Personal Growth and Purpose in Life subscales of Ryff’s Psychological Well-Being Scale, the Social Provisions Scale, and the Generalized Self-Efficacy Scale, respectively). Participants will be re-assessed on these measures after 6 months.

**Discussion:**

The results of this randomized controlled trial will generate new knowledge relating to the physical and psychological health benefits of different levels and types of volunteering for older people. In addition, insight will be provided into the major factors influencing the recruitment and retention of older volunteers. Understanding the full potential for volunteering to affect physical and mental well-being will provide policy makers with the evidence they require to determine appropriate investment in the volunteering sector, especially in relation to encouraging volunteering among older people who constitute an important resource for the community.

**Trial registration:**

Australian and New Zealand Clinical Trials Registry ACTRN12615000091505. Date registered: 3 February, 2015.

## Background

In Australia, consistent with global trends, there is a marked ageing of the population. Those over the age of 65 currently constitute 14.0 % of the population [1]. By 2061, more than one in five Australians will be over the age of 65, with the fastest rate of growth being among those over 85 [2].

As the population ages, the increasing incidence of age-related illnesses will have significant economic and social cost implications [3,4]. For example, older age is associated with higher body mass index scores [5,6], indicating that as the population ages, the economic and health-related costs associated with obesity will escalate. Older people also tend to engage in lower levels of physical activity than other population segments [7], and are thus in need of programs that can motivate and facilitate their engagement in higher levels of activity. As a result of their greater susceptibility to a wide range of health problems, older people have been recognized as a group requiring particular attention in the design of health promotion and illness prevention programs [8,9].

A growing evidence base demonstrates that interventions that focus on physical and social activities can assist in preventing and treating both physical and mental health problems [10-14]. There is also an emerging body of knowledge relating to sedentary time as an independent risk factor for physical illness, in particular cardiometabolic diseases [15-17]. To date, however, there appears to be no research investigating the effects of being sedentary on mental health, nor the impacts of volunteering on sedentary time. This study will explore the potential for interventions involving volunteer activities to produce positive physical and mental outcomes for older people, thereby contributing to the limited evidence relating to the potential of volunteering as a health intervention.

### Volunteering

Volunteering is defined as work activities that are unpaid, non-compulsory, and unrelated to family obligations [18]. ABS [19] data indicate that around a third of Australians engage in some form of volunteering within a 12-month period, with the highest rates among those aged 55–64 years (46 %) and 65–74 years (38 %). Previous studies suggest that volunteering has substantial health benefits for older people (for reviews see [20-22]). While causality is difficult to demonstrate due to the largely observational nature of data synthesized in reviews, evidence suggests that engaging in volunteering activities may provide beneficial social, physical, and cognitive outcomes for older people [23-32].

Volunteering has also been linked with higher levels of self-rated health, lower mortality rates, reduced risk of depression, and improved psychological well-being [20,30,33-38]. One of the mechanisms by which health benefits are produced by volunteering may be an increase in physical activity [39], which is likely to be largely due to additional manual work and walking [29]. However, there is a lack of physical evidence of this relationship, and little understanding of why it exists [31] and which forms of volunteering are most effective in generating positive health effects [40].

Motivational studies consistently demonstrate that an advantage of volunteering is that it gives older individuals an increased sense of meaning [24,41]. In a study of seniors’ conceptions of well-being [42,43], results showed that older people are interested in undertaking activities that are of benefit to others and that volunteering is salient in their deliberations about how they could achieve this outcome. However, a primary barrier was reported to be a lack of knowledge regarding volunteering opportunities and how they can be accessed. There appears to be a preference for word-of-mouth communications about volunteering opportunities, especially in the form of direct invitations to assist with specific tasks [44-46].

Volunteering is similar to physical activity in that participation rates are highest among those in better health and with higher levels of income and education [47]. It is also similar in that individuals are likely to assess the costs and benefits associated with the activity in their commencement and continuation decisions [48]. Unfortunately, little is known about how these decisions are made, and more research is needed to understand this phenomenon. Older people need particular consideration when developing health promotion messages because of their greater heterogeneity due to more extensive and varied life experiences, their stronger health-related motivations, and the physical deterioration that occurs with age that affects message processing [43,49-51]. However, little is known about the most effective ways to communicate with older people with the specific purpose of motivating them to engage in activity in general and volunteering activities in particular [52,53]. In the case of physical activity, it has been suggested that focusing on the social benefits may be more effective than emphasizing the physical health benefits [54,55]. It is likely that a similar focus on social benefits in messages aiming to encourage volunteering behaviors may be effective with the target group. As older people appear to consider mental incapacity as being more undesirable than physical incapacity [56], another approach may be to highlight the mental health benefits of participation in volunteering behaviors.

In summary, a growing body of research demonstrates the importance of combining physical, cognitive, and social activities to achieve healthy ageing. Volunteering can facilitate these activities and thus may have positive outcomes for older people. Little previous work has quantified the physical health benefits of volunteering, and even less has investigated the mental health benefits. In addition, previous studies have tended to use self-report data rather direct health measures [30]. Understanding the full potential for volunteering to affect physical and mental well-being will provide policy makers with the evidence they require to determine appropriate investment in the volunteering sector, especially in relation to encouraging volunteering among older people who constitute an important resource for the community.

The aim of this study is to assess the relative and combined effects of volunteering on seniors’ physical and mental well-being. This aim will be achieved in the context of a randomized controlled study using an Australian population sample. The primary research objective is to test whether engagement in a volunteering program results in significant improvements to physical and mental health compared to control (usual lifestyle activities). The results can be used to inform public policy on this issue and develop appropriate strategies to encourage older people to participate in volunteer activities.

## Methods/Design

The trial is funded by an ARC Discovery Grant (DP140100365) and has received ethical approval from Curtin University’s Human Research Ethics Committee (Approval reference: HR21/2014). It is a single-blind, randomized controlled trial designed to assess the impact of volunteering on seniors’ physical and mental well-being. Participants who consent will be randomized on a 1:1 basis to one of two conditions: control versus volunteering intervention.

### Sample

#### Eligibility

Table 1 summarizes the criteria used to determine participant eligibility. Potential participants must be aged 60 years or older and not have engaged in volunteering activities during the previous 12 months. Potential participants will be advised that volunteering constitutes work activities that are unpaid, non-compulsory, and unrelated to family obligations and charitable giving [18]. Those in paid employment will be excluded because their workplace participation is likely to confer physical and mental health benefits that cannot be accessed by their nonworking peers [26,57]. Non-working individuals are also likely to have the most to benefit from interventions designed to increase their physical and mental well-being due to their greater likelihood of isolation [58,59]. Potential participants will be advised that they need to be adequately mobile and physically fit to undertake the physical health tests.

**Table 1 Tab1:** Inclusion and exclusion criteria

Inclusion criteria	Exclusion criteria
Fully retired	In paid employment
Age 60+	Age <60
Nil formal/regular volunteer work in last 12 months	Formal/regular volunteer work in last 12 months
Mobility and basic functional fitness	Mobility or functional fitness issues

#### Recruitment procedures

To maximize the heterogeneity of the sample, recruitment strategies will include (i) placement of notices in community newspapers and seniors’ publications, (ii) community radio announcements, (iii) distribution of flyers at seniors’ events and retirement villages, and (iv) notices distributed via local government and non-government organizations that have representation across the metropolitan area (e.g., the Council of the Aged and the Seniors Recreation Council). These varied recruitment methods will increase the likelihood of attracting a diverse sample in terms of age, gender, and socioeconomic status.

The recruitment notices will call for those aged 60+ to participate in “a study on seniors’ health”. Those who express an interest will be given details of the study and screened for their eligibility. While participants will be aware that the study relates to health among older Australians, they will be blinded to the exact nature of the research project (i.e., the existence of the intervention and control groups and the comparison of outcomes between them). Upon debriefing at the end of the study, participants will be advised of the two conditions and the full purpose of the study. At this stage, those in the control condition will be given the opportunity to consult with a volunteer agency representative should they wish to commence volunteering once they become aware of the intervention nature of the study.

Participants will be remunerated via two payments of $100, one given at baseline assessment and one at the 6-month follow-up. It will be made clear to participants via the participant information sheet and verbally that they will be compensated for their contributions to the study and that the payment is given for them to use for any expenses incurred as a result of participating.

#### Sample/Randomization

In line with samples used in previous related research [29,31], 400 retired/non-employed individuals in good health aged 60+ years will be recruited into the study. A power calculation was carried out in G*Power to calculate the required sample size for power of 0.80 to detect any main effect or interaction at an alpha level of 0.01 and a conservative effect size of 0.1. A sample size of 370 (1:1 allocation) will be sufficient to detect a difference in effects between groups at post-intervention. These numbers take into account a loss of 25 % of participants during the course of the study. Allowing for potential effects of various extraneous influences, such as protocol adherence, 200 participants per group will be required (total n = 400).

After being screened for eligibility, half the sample will be randomly assigned to an intervention group (*n* = 200) and half to a control group (*n* = 200). The randomization process will be conducted using a computer-generated randomization script by a researcher who is blinded to the nature of the study and independent from participant recruitment and data collection/analysis processes.

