##### Primary analyses

The primary analyses will utilize a between groups design with two time points (baseline and post-intervention) and two groups (volunteer vs. control). The primary independent variable is therefore condition. Relevant analyses (e.g., multivariate analyses of covariance) will be performed to explore pre to post differences in measures of physical and psychological health while controlling for baseline scores on those variables and any other relevant confounders (e.g., control group members engaging in increased physical activity because recommended to do so by their medical practitioners). An alpha level of *p* < .05 will be the criterion for significance in all statistical comparisons. Estimates of effect size will also be calculated.

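### The claim of 80% power for any main effect or interaction at an effect size of 0.1 does not hold for the group main effect, and the 0.1 is given without metric, contrast or correlation

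*Protocol article*

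**What the plan says.** Under Sample/Randomization, the protocol article reports a G*Power calculation for power of 0.80 "to detect any main effect or interaction at an alpha level of 0.01 and a conservative effect size of 0.1". It concludes: "A sample size of 370 (1:1 allocation) will be sufficient to detect a difference in effects between groups at post-intervention". On dropout it adds: "These numbers take into account a loss of 25 % of participants during the course of the study". The total is then raised to 400, 200 per group, to allow for influences such as adherence. The section does not say which G*Power test was run, whether 0.1 is an f, a d or something else, which contrast it describes, or what correlation between baseline and follow-up was assumed.

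Under Primary analyses, the article says: "The primary analyses will utilize a between groups design with two time points (baseline and post-intervention) and two groups". The example given there is multivariate analysis of covariance, controlling for baseline scores, with significance judged at .05.

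**The concern.** One sample size is said to serve every main effect and every interaction at a single effect size. In a two-group, two-time-point repeated-measures design this is generally impossible. A positive correlation between time points makes within-person contrasts more precise and the between-group average less precise, so the same f needs very different numbers.

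The word conservative adds a second problem. With no metric or contrast attached, a reader may take 0.1 as f for a comparison of the two groups at six months, which is a difference of 0.2 SD. If the calculation was really for the interaction, the effect it covers is twice that size. The trial is meant to inform volunteering policy, and a null result could then be taken as evidence against a small benefit that the trial had limited power to detect.

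**Working it through.** **Inputs from the protocol article.** Power 0.80; alpha 0.01 for the sample size and .05 for the analysis; effect size 0.1; two groups, 1:1; two time points; 25% loss; stated N of 370, raised to 400. Expected completers: 400 x 0.75 = 300.

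**Assumptions, not in the article.** The 0.1 is Cohen's f. The correlation between time points (rho) is 0.5 for the reproduction and is varied afterwards. All powers use the noncentral F distribution with 1 numerator df.

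**1. Reproducing 370.** For the time-by-group interaction, and equally for the time main effect, with m = 2 time points:

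lambda = N x m x f² / (1 − rho) = N x 2 x 0.01 / 0.5 = 0.04 N

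Power is 0.798 at N = 294 and 0.801 at N = 296, so 296 are needed. Then 296 x 1.25 = 370, exactly the stated figure. (Dividing by 0.75 instead gives 395, which the final 400 covers.)

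**2. Group main effect, same f and rho.**

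lambda = N x m x f² / (1 + rho) = N x 0.02 / 1.5 = 0.0133 N

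This needs N = 880. Power is 27% at 296 and 28% at 300.

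**3. Can another correlation rescue the claim?** Analysable N for 80% power at f = 0.1:

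| rho | Interaction or time, alpha .01 | Group, alpha .01 | Interaction or time, alpha .05 | Group, alpha .05 |
|---|---|---|---|---|
| 0 | 588 | 588 | 396 | 396 |
| 0.3 | 414 | 764 | 278 | 514 |
| 0.5 | 296 | 880 | 200 | 592 |
| 0.7 | 180 | 998 | 120 | 670 |
| 0.8 | 122 | 1,056 | 82 | 710 |

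The group requirement is lowest at rho = 0 and rises from there. Even that minimum exceeds 300 at either alpha.

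**4. What f = 0.1 means for the interaction.** In a 2x2 layout the interaction cell effects are ±(difference in change)/4. Setting (difference in change)/4 = 0.1 SD gives a difference in change of 0.4 SD. Check: a two-group comparison of change scores has lambda = N x 0.4² / (4 x 2(1 − rho)), which at rho = 0.5 is 0.16 N / 4 = 0.04 N, as in step 1.

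**5. If 0.1 is read as f for the six-month group difference (0.2 SD).** For baseline-adjusted ANCOVA with baseline correlation r:

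lambda = N x f² / (1 − r²)

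At alpha .01 this needs 880 completers for r = 0.5 and 600 for r = 0.7. With 300 completers:

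| Assumed r | Power for 0.2 SD, alpha .01 | Power for 0.2 SD, alpha .05 | Difference detectable with 80% power, alpha .01 | Same, alpha .05 |
|---|---|---|---|---|
| 0.5 | 28% | 51% | 0.34 SD | 0.28 SD |
| 0.7 | 44% | 68% | 0.28 SD | 0.23 SD |
| 0.8 | 62% | 82% | 0.24 SD | 0.20 SD |

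**The case against.** **The metric and correlation are inferred.** This stands. The exact match of 296 x 1.25 is strong evidence, but it is not proof. A multivariate effect size f² of 0.1 would also land close to 370: 16 outcomes need 277, and 277/0.75 = 369; 19 outcomes need 295, and 295 x 1.25 = 369. The article lists many primary outcomes and names a multivariate analysis, so this route is possible. It is less natural, and nothing in the text states it.

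**The sentence about 370 may be correct.** A reader might infer that the statement about a post-intervention difference is simply false. The document does not support that. The sentence can describe the interaction itself. With equal baselines that is a 0.4 SD difference at follow-up, for which ANCOVA with 300 completers has 92% power at alpha .01 (r = 0.5). The sentence fails only if 0.1 is carried over to the follow-up contrast.

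**The 370 does not fit the interaction alone.** The time main effect needs the same 296. It is the group main effect that breaks the blanket claim. In a pre/post trial that effect averages over baseline and is not the natural test of treatment. This limits the practical harm, but the claim as printed still covers it.

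**The trial may detect smaller effects.** A reader might infer that it can detect only 0.3 to 0.4 SD. That is too strong. At the planned alpha of .05 the detectable difference is 0.23 SD at r = 0.7, and at alpha .01 it is 0.24 SD at r = 0.8. Measures such as BMI, girth and strength may plausibly have high baseline correlations, though the article gives none.

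**The planned model is only an example.** The article offers multivariate analysis of covariance as an illustration. Univariate ANCOVA is used here as a simple stand-in for adjustment for baseline.

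**Conclusion.** The concern holds in limited form. Reading 0.1 as Cohen's f, the claim of 80% power for every main effect and interaction is not met: the group main effect has about 28% power with 300 completers at rho = 0.5 and alpha .01, and no correlation from 0 upward brings both it and the interaction to 80%. That second result does not depend on the assumed 0.5.

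Describing 0.1 as conservative is misleading because it lacks a metric and contrast. As an interaction it is 0.4 SD in change. As a follow-up difference it is 0.2 SD, where power runs from 28% to 62% at alpha .01 and from 51% to 82% at alpha .05, over assumed baseline correlations of 0.5 to 0.8. Whether 0.4 SD is a large effect for this intervention cannot be judged from the document. The defect lies in the stated power; nothing here shows that the enrolment target must change.

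**What to change.** In Sample/Randomization, delete the claim covering any main effect and the word conservative. State the metric of the effect size, the contrast it refers to and the G*Power test used. Then restate the detectable difference under the baseline-adjusted model of the Primary analyses section, marking the correlation as an assumption. Suggested content: with 300 completers and 80% power, the detectable between-group difference at six months is 0.28, 0.23 or 0.20 SD at the planned two-sided alpha of .05, for assumed baseline correlations of 0.5, 0.7 or 0.8. If alpha 0.01 is kept for the sample size, give 0.34, 0.28 and 0.24 SD alongside.

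The cost is one rewritten passage and a stated figure that looks less favourable. Enrolment, allocation and analysis do not change.

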#### Procedure

Consenting participants will be contacted to arrange a physical assessment and face-to-face interview. The assessments/interviews will be conducted on the campuses of two of the institutions involved in the study. These campuses are located 37 km apart and hence provide wide geographical coverage of the Perth metropolitan area.

Prior to arriving for their interview, participants will be asked to complete a battery of psychological and physical health status questionnaires. Sociodemographic information (age, gender, socioeconomic status, marital status, and ethnicity) will also be collected. Those participants with a preference for using the Internet and who have access to a computer will be asked to complete the questionnaires online. Participants without access to a computer will be posted out a paper version to be returned via a reply paid envelope or bring to their first interview. The instruments that will be used to collect psychological data from participants are listed in Table 2. The information and consent forms will be included at the front of the online survey for those participants using the internet, and paper copies of the information and consent forms will be included with the paper surveys that are posted out.

**Table 2 Tab2:** Psychological measures used in the assessment protocol (primary and secondary)

Outcomes	Instruments
